#### Methods for additional analyses (e.g., subgroup analyses) {20b}

Subgroup analyses that are envisioned at the conclusion of this study will include exploratory analyses for outcomes among patients by lens status (i.e., aphakic, phakic, pseudophakic), by macula status (i.e., on, off, split), and by the presence of an inferior RD. Adjustments for multiple comparisons will not be performed for these subsequent analyses.

#### Methods in analysis to handle protocol non-adherence and any statistical methods to handle missing data {20c}

Outcomes will be analyzed as randomized. Missing data will be handled using multiple imputation.

#### Plans to give access to the full protocol, participant-level data and statistical code {31c}

The full protocol will be published in the journal *Trials*. The final trial dataset could be made available to other research teams upon reasonable request and after evaluation of the request by the trial team. The shared dataset will be coded and will not include any identifying patient data.

### Oversight and monitoring

#### Composition of the coordinating center and trial steering committee {5d}

The trial steering committee is composed of research assistants, coordinators, nurses, and ophthalmologists and will meet bi-monthly and on an as-needed basis to discuss the advancement of the trial and address any difficulties in participant recruitment.

#### Composition of the data monitoring committee, its role and reporting structure {21a}

A data monitoring committee will not be required for this trial given that it will involve a relatively small number of patients and compare procedures that are already part of the standard of care.

#### Adverse event reporting and harms {22}

All adverse events (defined as a deviation from the ideal postoperative evolution) will be reported in the trial using the novel Classification of Ophthalmological Complications (COC; see Table 1) to be able to capture the severity of all complications.

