#### Intervention description {11a}

Surgery will be performed under local anesthesia with retrobulbar block (5 to 10 cc of 2% lidocaine without epinephrine and 0.5% bupivacaine in a 1:1 ratio). In all cases, surgery will be performed using a wide-angle viewing system and the Alcon Constellation System (Alcon Laboratories, Inc., Fort Worth, TX) combined with the ULTRAVIT 23-G + or 25-G + vitreous cutter (Alcon).

Pars plana vitrectomy will be performed in a standard fashion starting with central vitrectomy, then by localizing retinal breaks and marking them with endodiathermy. Perfluorocarbon will be used to displace subretinal fluid which will be aspirated at its exit from the retinal break as much as possible to avoid retinal pigment epithelium (RPE) dispersion into the vitreous and maximal vitreous base shaving will be performed in all cases. This will be followed by an air-fluid exchange. The use of cryotherapy to solidify the retina intraoperatively and the use of internal limiting membrane peeling of the posterior pole will be at the discretion of the surgeon. In all cases, laser photocoagulation around retinal breaks, holes, areas of lattice degeneration, and posterior to sclerotomy sites will be done and then a 360° laser retinopexy will be performed at the surgeon’s discretion and consisted of three rows of medium-white burns anterior to the level of the vortex vein, towards and beyond the equator. In cases with SB, after 360° peritomy and dissection in 4 quadrants, a 41-circling band with 3082 sleeves (Labtician Ophthalmics, Oakville, ON, Canada) will be used in all cases and fixed to the sclera at approximately 11.5 mm from the limbus (or 5.5 from the insertion of rectus muscles) using partial thickness scleral tunnel or mattress sutures with 5.0 prolene or nylon performed in four quadrants depending on the surgeon preferences. At the end of the surgery, a gas tamponade will be injected inside the eye, either SF_6_ or C_3_F_8_. The surgical technique at the second surgery, if applicable, will be at the discretion of the treating surgeon.

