### Outcomes {12}

The primary outcome is SSAS defined as freedom from reoperation for recurrent RRD at all follow-up evaluations. Localized recurrences or new tears treated using a laser in the ambulatory clinic will not be considered a failure of the primary surgery but will be noted. We considered a difference of 10% in SSAS to be clinically relevant for this trial and based the sample size calculation on this threshold of chosen efficacy. Secondary outcomes will include PHVA at 8–10 weeks and 6 months, final BCVA, final retina status (i.e., attached or detached), time to onset of RD recurrence, severity and number of complications, and questionnaire results (see Additional file 1). The principal questionnaire was previously used and validated by Potic et al. [12] with additional questions used to specifically assess possible side effects and reductions in quality-of-life associated with the addition of SB and longer-duration intraocular gases. In cases of primary surgery failure, the cause of recurrence (i.e., PVR including epiretinal membrane (ERM) in the macular area causing recurrent RD, new or recurrent retinal breaks) will be reviewed. The extent of PVR at follow-up will also be evaluated. The duration of surgery will also be collected. Number of additional visits and supplementary laser and intraocular pressure treatments will be evaluated. Complications will be graded using the novel Classification of Ophthalmological Complications (COC; see Table 1).

**Table 1 Tab1:** Classification of ophthalmological complications (COC)

Complication grade	Definition
Grade I	Any deviation from the normal postoperative course without the need for modification of planned pharmacological treatment or surgical intervention Allowed therapeutic regimens are as follows: any previous medication, any medication prescribed routinely (i.e., topical antibiotics, glaucoma drops, anti-inflammatory drops, steroid drops, oral pills), artificial tears, hot compresses, and analgesic drugs (Advil/Tylenol only)
Grade II	Requiring change in planned pharmacological treatment with higher frequency or longer duration of drops or the introduction of new drugs (including autologous serum drops); these can include glaucoma drops and steroid drops and the use of oral drugs other than Advil/Tylenol (e.g., Diamox, prednisone). Also includes YAG capsulotomy

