Grade III	Requiring any laser procedures other than YAG capsulotomy or any periocular/intraocular injections. Simple interventions performed at the slit lamp (e.g., AC burp or tap, AC filling, epithelial debridement) or under local anesthesia not requiring an OR setup (e.g., pneumatic retinopexy, keratectomy, leaking wound requiring additional suture) are also included
Grade IV	Requiring intervention with an OR setup or requiring pharmacological treatment with intravenous drugs or hospitalization
Grade V	Sight-threatening complication or loss of eye (endophthalmitis, globe rupture, suprachoroidal hemorrhage)
Grade Va	Unilateral sight-threatening complication or loss of eye (endophthalmitis)
Grade Vb	Bilateral sight-threatening complication or loss of eyes (bilateral endophthalmitis, bilateral eye trauma, sympathetic ophthalmia)
Grade VI	Life-threatening complications (including CNS complications) requiring IC/ICU management
Grade VII	Death

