### Participant timeline {13}

Table 2 illustrates the patient timeline for the study. Preoperative baseline characteristics will include age, sex, symptoms duration, pinhole visual acuity (PHVA) at presentation in metric Snellen notation defined as the best visual acuity obtained using the patient’s current refraction with or without improvement with pinhole, laterality of presentation, myopia greater than four diopters, lens status (i.e., aphakic: patient without their native crystalline lens or an intraocular lens; phakic: patient with their native crystalline lens; pseudophakic: patient with an intraocular lens replacing their native crystalline lens), macula status (i.e., on, off, split), RD extent in clock hours, number of retinal breaks assessed preoperatively and under direct intraoperative visualization, and inferior retinal breaks in the detached retina between 4:00 and 8:00 clock hours. Patients will be assessed at 1 day postoperatively, 2 weeks, 8–10 weeks, 6 months, and 12 months and any additional follow-ups as needed on an emergent basis. At each scheduled follow-up, visual acuity will be assessed using a Snellen visual chart with pinhole and intraocular pressure measured by Goldmann applanation, iCare, Accupen, and Tonopen. LOCS III grading for cataract development will be used to evaluate patients’ lens at each follow-up. Multimodal imaging using macular optical coherence tomography (OCT), optic nerve/retinal nerve fiber layer (RNFL) OCT, ganglion cell layer (GCL) OCT measures, OCT angiography, widefield fundus photography, and fundus autofluorescence will be conducted when it is possible (after gas disappearance at 6 months and 12 months). Starting at the 8–10-week follow-up, autorefraction will be used. Quality of life questionnaires will also be administered to patients at each follow-up starting at the 2-week postoperative follow-up.

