### Data collection and management

#### Plans for assessment and collection of outcomes {18a}

Trained and designated research team members will be responsible for collecting baseline and outcomes data with standardized methods of PHVA measurement and questionnaires. A training session of an hour will be provided to each research team member by a single investigator (MH) to promote data quality.

Regarding the intraoperative description of the RRD, a standardized RRD reporting form will be filled out by each treating surgeon at the time of the operation.

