### Statistical methods

#### Statistical methods for primary and secondary outcomes {20a}

The primary outcome will be compared between the groups using the chi-square test for the difference in rates of SSAS in both the surgical technique and gas tamponade arms of the study. Testing between the groups for secondary outcomes of PHVA at 8–10 weeks and 6 months, final BCVA, final retina status (i.e., attached or detached), time to onset of RD recurrence, severity and number of complications, and questionnaire results will also be performed using adjustments for repeated measures and multiple comparisons as appropriate.

To calculate estimates of the treatment effects and their corresponding 95% confidence intervals (CI), a multiple logistic regression including both surgical technique and gas tamponade will be built for SSAS. Cox proportional hazards and multiple linear regression models will also be built for the time to onset of RD recurrence and final BCVA, respectively. In these analyses, we assume that there is a negligible interaction between surgical technique and gas tamponade. However, appropriate interaction terms will be added to the models to explore this possibility. If this shows negligible interaction, both analyses will be performed independently.

Statistical analyses will be performed using R for Windows (version 3.6.3; R Foundation for Statistical Computing) and IBM SPSS Statistics for Windows (version 27.0; IBM Corp., Armonk, NY). Analyses will be conducted at the 0.05 significance level, except when appropriate for adjustment of multiple comparisons.

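### Adverse events and COC Grade I are defined by the postoperative course alone, so intraoperative complications resolved at the index operation are not adverse events in either arm, including some specific to the buckle

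*Protocol article*

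**What the plan says.** The section Adverse event reporting and harms {22} gives its own definition: "All adverse events (defined as a deviation from the ideal postoperative evolution) will be reported in the trial". It names the Classification of Ophthalmological Complications (COC) as the reporting scale.

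The COC is Table 1 in Outcomes {12}. Its lowest grade has the same anchor: "Any deviation from the normal postoperative course without the need for modification of planned pharmacological treatment or surgical intervention". The higher grades are defined by the treatment needed or by severity, without words on timing. Grade IV, for example, is "Requiring intervention with an OR setup or requiring pharmacological treatment with intravenous drugs or hospitalization".

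The severity and number of complications form one of several secondary outcomes in {12}. Statistical methods {20a} plans between-group testing of them; the sentence reads in part "severity and number of complications, and questionnaire results will also be performed using adjustments for repeated measures and multiple comparisons". Objectives {7} hypothesises fewer complications with PPV than with PPV-SB.

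Two places mention what is recorded at surgery. Participant timeline {13} lists the "number of retinal breaks assessed preoperatively and under direct intraoperative visualization". Plans for assessment and collection of outcomes {18a} says: "Regarding the intraoperative description of the RRD, a standardized RRD reporting form will be filled out by each treating surgeon".

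**The concern.** The primary randomised question is whether to add an operative step. Some harms of an operative step occur in the operating room and are put right there. A definition that begins with the postoperative period does not count these when the recovery is ideal.

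At stake is the completeness of the harms comparison by technique. Intervention description {11a} gives PPV-SB eyes steps that PPV eyes do not have: peritomy, dissection in each quadrant, and fixation of the band "using partial thickness scleral tunnel or mattress sutures with 5.0 prolene or nylon performed in four quadrants". Strategies to improve adherence {11c} does not permit the allocation to change in the operating room. A resolved event of these steps therefore has no counterpart in the PPV arm, and leaving it out removes harm specific to the buckle from the comparison. The Discussion says that the trial will address whether a supplemental buckle is justified, and such harm belongs in that judgement.

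**Working it through.** The plan states no figure on this point, and the document gives no complication rates. The check is therefore mainly one of wording.

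**Step 1. Which intraoperative events are lost?** Sort them by what follows.

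| Intraoperative event | Adverse event under {22}? | Gradable on the wording of Table 1? |
|---|---|---|
| Followed by a postoperative deviation | Yes | Yes |
| Ideal recovery, but needed a drug change, extra laser or OR intervention, or was sight-threatening | No | Yes: Grades II to VII have no timing limit |
| Ideal recovery, resolved without any of these | No | No: only Grade I could take it, and Grade I is postoperative |

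The third row is lost on both readings. The second depends on which text governs, because {12} says that complications are graded by the COC without repeating the definition in {22}.

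**Step 2. Is the line between the rows clear?** Not fully. A repair made during the index operation could be read as an intervention with an operating-room setup. Two assessors could then score the same minor event as nothing or as Grade IV.

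**Step 3. Which arm loses events?** Vitrectomy is done in both arms, so resolved vitrectomy events can be lost in both. The buckle steps exist only in PPV-SB, so resolved buckle-step events can be lost only there.

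**Step 4. Does the net direction follow?** Let *b* be the rate per PPV-SB eye of resolved buckle-step events. Let *s*(SB) and *s*(PPV) be the rates of resolved vitrectomy events in the two arms, and let *d* = *s*(SB) − *s*(PPV). The amount omitted from the difference PPV-SB minus PPV, in mean number per eye, is

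(*s*(SB) + *b*) − *s*(PPV) = *b* + *d*.

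If *d* = 0, shared events cancel and the omission understates PPV-SB harm by *b*. The protocol does not fix *d* at zero, because several vitrectomy steps are left open; for instance, "the use of internal limiting membrane peeling of the posterior pole will be at the discretion of the surgeon".

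Two assumed cases show that the sign is open:
- *b* = 0.04, *d* = +0.02: 0.04 + 0.02 = 0.06 per eye, an understatement of PPV-SB harm.
- *b* = 0.01, *d* = −0.02: 0.01 − 0.02 = −0.01 per eye, a slight overstatement.

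For scale, Sample size {14} gives 560 / 2 = 280 eyes per technique arm. Each percentage point of *b* is then 280 × 0.01 = 2.8 events. All values of *b* and *d* are assumptions.

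**Step 5. Does another section repair the definition?** No. The form in {18a} is introduced for describing the detachment, and the intraoperative item listed in {13} is the count of breaks. Neither changes what counts as an adverse event. The fields of the form are not shown, so it may already have a place for complications.

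**The case against.** The best case against the point has four parts.

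- *The definition treats both arms alike.* This stands. A reader might infer that the gap falls only on PPV-SB. It does not: the definition drops resolved vitrectomy events in both arms, and only the buckle-specific part is one-sided. That part is one-sided simply because only one arm has the step.
- *Most events that matter can already be graded.* This stands in large part. Grades II to VII have no timing limit, and any event with a postoperative consequence is captured. It leaves the third row of the table above, and the unclear reading of Grade IV.
- *The operative form may already record complications.* This also stands. A reader might infer that the data will be missing, but the document does not show that. The form's contents do not, however, alter the definition stated in {22}.
- *This is detail for an analysis plan or case report form.* This does not stand. The article does not leave the definition to another document; it states one, and that definition suits a comparison of operative techniques poorly.

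A reader might also see a contradiction with the statement in {22} that the scale serves to capture the severity of all complications. Those words can be read as referring to the events just defined, so no contradiction is shown.

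**Conclusion.** The point holds as a minor weakness in a stated definition. As written, an intraoperative complication resolved at the index operation and followed by an ideal recovery is not an adverse event in either arm. The comparison of complications may therefore omit some harm specific to the buckle.

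The omitted set is narrow. Its size cannot be derived from the document, and neither can its net direction, because the difference in resolved vitrectomy events is unknown. It would be tempting to say that the plan is biased against finding the hypothesised advantage of PPV on complications. That follows only if resolved vitrectomy events are equally frequent in the two arms, or nearly so, which the document does not establish. Nor does the document support any statement of how far the test on this outcome would move.

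SSAS is unaffected, since it depends on reoperation for recurrent detachment. The conclusion rests on reading {22} and Grade I literally.

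**What to change.** In {22}, define an adverse event as *a deviation from the ideal intraoperative or postoperative course*. Then:

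1. Record intraoperative complications in both arms on the existing operative form ({18a}), after checking that it has a field for them.
2. Keep the main COC grading as planned. Report intraoperative complications by technique arm in a separate table within the complications outcome.
3. Add one sensitivity analysis that includes them in the complication count. For that analysis, read Grade I as covering the intraoperative or postoperative course, do not count the index operation itself as the intervention of Grade IV, and count each event once, under its COC grade if it also has a postoperative consequence.

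The cost is a few words, possibly one form field, one table and one analysis. The downside is that these events are reported by the operating surgeon, who is not blinded ({17a}). The separate table keeps that source visible and leaves the main grading untouched. Recruitment is planned to run to July 2027, and such events are best recorded at surgery, so an early change is worth more than a later reconstruction.

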#### Frequency and plans for auditing trial conduct {23}

The Research Ethics Board (REB) of the CHU de Québec – Université Laval reserves the right to audit the trial conduct in an independent process from the investigators and funders. However, no predetermined audits will be pre-planned.

#### Plans for communicating important protocol amendments to relevant parties (e.g., trial participants, ethical committees) {25}

Important protocol amendments will be obligatorily communicated to the Institutional Review Board of the CHU de Québec – Université Laval and reported in the trial registration on ClinicalTrials.gov. If these amendments pertain to trial participants and affect their participation in the study, these will also be communicated to them.

#### Dissemination plans {31a}

The results of this trial and any secondary analyses will be reported through a presentation in ophthalmology and/or subspecialty retina conferences, as well as publication in ophthalmology and/or subspecialty retina peer-reviewed journals.

## Discussion

This will be the first 2 × 2 factorial RCT examining repair techniques in primary RRD. It will also be the first RCT to compare gas tamponade between the two most common agents. Notably, it will be adequately powered to detect an effect size as that reported in the PRO study if this difference between treatments truly exists. The use of multimodal imaging will also be a novel aspect of this study, allowing us to compare head-to-head the impact of adding an SB to the retina’s recovery after RRD repair and of differing gas tamponades.

Primary RRD affects approximately 6.3 to 17.9 per 100,000 population [15] and can cause important visual impairment if not corrected promptly. Patients who undergo phacoemulsification with intraocular lens implantation for symptomatic cataract are also at greater risk of developing RRD subsequently. The number of patients affected by RRD is therefore expected to increase in the coming years. Until now, the treatment of RRD has been largely guided by pragmatic retrospective cohort studies. There is a lack of strong evidence guiding therapeutic decisions, and this trial will address (1) whether supplemental SB is justified and (2) whether longer duration gas tamponade with C_3_F_8_ is necessary.

## Trial status

Protocol version 4; October 31, 2023. Recruitment start date: September 2023; approximate recruitment end date: July 2027.

## Data Availability

The principal investigator and co-investigators will have access to the final trial dataset. This could be made available to other research teams upon reasonable request and after evaluation of the request by the trial team.

## Abbreviations

BCVA: Best-corrected visual acuity
C_3_F_8_: Perfluoropropane
CHU: Centre Hospitalier Universitaire
CI: Confidence interval
COC: Classification of Ophthalmological Complications
ERM: Epiretinal membrane
ETDRS: Early Treatment Diabetic Retinopathy Study
GCL: Ganglion cell layer
OCT: Optical coherence tomography
OCT-A: Optical coherence tomography angiography
PHVA: Pinhole visual acuity
PPV: Pars plana vitrectomy
PPV-SB: Pars plana vitrectomy with scleral buckle
PVR: Proliferative vitreoretinopathy
RD: Retinal detachment
REB: Research ethics board
RNFL: Retinal nerve fiber layer
RPE: Retinal pigment epithelium
RRD: Rhegmatogenous retinal detachment
SB: Scleral buckle
SF_6_: Sulfur hexafluoride
SSAS: Single-surgery anatomic success
